| **Secondary**  **outcomes** | - Cumulative Pregnancy Rate (CPR) - Time to pregnancy and live birth - Miscarriage rate - Reproductive outcomes per IVF cycle, - Rate of recurrent implantation failure (RIF) - Intra- and postoperative complications after surgery - Infections after oocyte pick-up - Quality of life - Pain - Health costs - Obstetrical outcomes and complications - P-progesterone at the day of frozen embryo transfer in HRT cycles |
| **Standard treatment** | First line ART |
| **Experimental**  **Treatment** | First line surgery followed by ART |
| **Duration of study**  **including follow up** | 6 years (inclusion 3 years and follow-up 3 years) |

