Reproductive outcome per IVF/ICSI-cycle: number of oocytes retrieved (mature and/or total), fertilization rate, Fresh embryo transfer (ET) (day 2, day 3, day 5), number of blastocysts cryopreserved, pregnancy rate per ET, live birth rate per ET, miscarriage rate per ET, cumulative pregnancy rate per cycle, cumulative miscarriage rate per cycle, cumulative live birth rate per cycle.

RIF (recurrent implantation failure) evaluated at the end of the study period. RIF is defined here as no pregnancy after three ETs in women <35 years and four ETs in women 35-39 years old (20).

Infections after oocyte pick-up will be registered yes/no and further classified as requiring i) treatment with antibiotics, ii) readmission or iii) surgical intervention.

Health related quality of life (HRQoL) and pain will be assessed by questionnaires, Endometriosis Health Profile (EHP-30), EQ5D and Numeric Rating Scale (NRS), completed by study participants preferably as electronical patient reported outcome measures or during the clinic visit (by manually filling in forms, by accessible computer or by mail). The assessments are performed maximum one month before the first intervention, at the time of oocyte retrieval, two months after ART or surgery and at three-year follow-up.

Intraoperative complications will be classified by Classic systems (21).

Two months postoperative complications will be defined according to the Clavien-Dindo (22) system.

Health care costs from randomization to end of trial: Direct costs will be used by assessing internal accounting and billing systems within the hospitals, cost per patient (CPP). We will also measure the quality-adjusted life years (QALYs) gained with the intervention and use this to undertake a cost-utility analysis. The QALY calculations will be based on fertility status measures for trial participants, with valuations of changes in fertility status and quality of life based on the EQ-5D.

Obstetrical outcomes and complications defined as:

- pregnancy- related complications: premature delivery, preeclampsia, gestational diabetes, placenta previa, placenta ablation, placenta spectrum disorders
- delivery-related complications: emergency caesarean section, pelvic floor trauma, delivery related bleeding, manual placenta removal

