- Uterine malformations (class U1-U6 according to ESHRE/ESGE-classification) (30)
- Patients with contraindications to surgery
- Patients undergoing ART with donated oocytes

RANDOMIZATION

After verification of eligibility, signed informed written consent participants will be randomly assigned to either undergo first-line ART or first-line surgery, followed by ART by equal allocation, 1:1. The randomization procedure will be stratified for participating center (permuted block design). Randomization will be performed at each site using the web-based instrument Red Cap. All inclusion criteria and no exclusion criteria must be met. One month before first treatment (IVF or surgery), inclusion and exclusion criteria are entered into the randomization/registration application RedCap. Patients withdrawn from the study after randomization but before treatment will be substituted by newly enrolled patients. Patients withdrawn from the study after first treatment will not be substituted. Username and password are required to log in; each investigator authorized to register patients has a personal login username and password. If all criteria are met, patients are registered, and the allocated patient number is recorded in the patients’ medical file.

There could be some uncertainty surrounding participants' willingness to engage in a Randomized Controlled Trial (RCT) comparing two fundamentally distinct approaches. Therefore, we intend to offer women who fulfill eligibility criteria but decline randomization the opportunity to take part in a parallel study – a prospective cohort study, that would provide valuable real-world outcomes of two different approaches to treatment of endometriosis -associated infertility. This parallel study will evaluate identical outcomes to those in the randomized trial. However, instead of random assignment, participation decisions will be made by the patients themselves, resulting in what is commonly referred to as a patient preference trial.

DEFINITION START OF TRIAL

Start of trial will be defined as start of first treatment which will be either surgery or first ART cycle (e.g start of FSH injections).

DEFINITION END OF TRIAL

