The study will end when all patients enrolled in trial have been followed for 3 years after first treatment, withdrawn consent, or are lost to follow-up. Data from study participants that are lost to follow will be included in the final analysis. The trial steering committee may end enrolment at any time if it is deemed that this is in the best interest of the patients.

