# STUDY TREATMENT

Time from randomization to first treatment (surgery or first ART cycle) should be minimized with a goal of three months and should preferably not exceed six months. Complications due to treatments (IVF or surgery) will be register in the eCRF and treated according to clinical routine at each hospital.

EXPERIMENTAL TREATMENT

First line endometriosis surgery followed by ART such as IVF or ICSI.

STANDARD/CONTROL TREATMENT

First line ART such as IVF or ICSI.

SURGICAL PROCEDURE

Surgery will be performed at one of four nationally specialized centers in advanced endometriosis surgery (Södersjukhuset Stockholm, Sahlgrenska University Hospital Göteborg, Skånes University Hospital, Malmö/Lund, Uppsala University Hospital). Intraoperative AAGL endometriosis staging, #ENZIAN classification and Endometriosis Fertility Index (EFI) (31) will be recorded in the study protocol. Surgery will be conducted according to the ESHRE recommendations of surgery in endometriomas and deep endometriosis (32, 33). Surgery should be multidisciplinary when needed (colorectal surgeons and urologists). The goal of the procedure is to remove as many endometriotic lesions as possible while also minimizing negative impact on organ function, since endometriosis is a benign disease. Rectal endometriosis will be removed with rectal shaving, discoid or segmental resection depending on the size and placement of the lesion in the rectal wall. Laparoscopic cyst enucleation is considered the "golden standard" as it is associated with a low recurrence rate, significant pain relief, and increased chances of spontaneous conception (34). In cases where ovarian reserve is already diminished, more gentle methods such as ablation therapy with CO2 Laser/Plasma Jet or sclerotherapy could be employed (35-37). These methods can also be used in combination with conventional surgical cyst enucleation. The choice of surgical technique should be tailored to the individual patient's needs.

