# PATIENT REPORTED OUTCOMES (PROMS)

When evaluating quality of life among women with endometriosis many different scales have been used, mostly of generic character that are not specific to the disease. One of these is 30-item Endometriosis Health Profile (EHP30), a scale that perform well in clinical practice in the routine evaluation of Health-Related Quality of life (HRQoL) The use of EHP30 is recommended by the National Board and Welfare in Sweden, the ASRM and ESHRE (40). Using EHP-30, a small study has shown an improvement in HRQoL in the follow-up after endometriosis surgery, an effect that may last for up to 6.8 years (41). Two recent studies show postoperative improvement in HQQoL measured by EHP-30 10 weeks and 3 months after surgery, respectively (42, 43). Especially women with deep endometriosis (DE) showed a more significant benefit from surgery (43). However, HRQoL can also be affected by infertility, and in this trial, infertility treatment will be delayed, thus, HRQoL is an important measurement.

POINTS OF ASSESSMENT

Baseline assessment will be obtained after randomization and maximum 1 month prior to surgery or start of first ART cycle

Thereafter assessment will be done prospectively at:

- 2 months after surgery (for the group randomized to first line surgery)
- 1:st oocyte pick up (for both randomization groups)
- 2 months after 1:st oocyte pick up
- 2:nd oocyte pick up
- 2 months after 2:nd oocyte pick up
- 3:rd oocyte pick up
- 2 months after 3:rd oocyte pick up
- Visit, phone call or questionnaire 3 years after randomization.

Compliance with completing the questionnaires will be investigated at each time point to

evaluate the procedure for data collection and the feasibility of the questionnaires.

INSTRUMENTS

The core questionnaire in EHP -30 includes 30 questions in 5 health-related areas: pain, control and powerlessness, emotional well-being, social support, and self-image. In addition, there are six supplementary modules covering work, relationship with child/children, sexual relationship, feelings about the medical profession, feelings about treatment and feelings about infertility.

The Numeric Rating Scale (NRS) is a frequently utilized pain assessment tool commonly employed in postoperative care. It allows for the momentary evaluation of pain on a scale from 0 to 10, with 0 representing "no pain" and 10 indicating "the worst pain imaginable”.

EQ-5D is a standardized non-disease specific instrument for describing and

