# HEALTH ECONOMICS

Health economics will be analyzed with respect to Swedish conditions first and with an international perspective.

DIRECT COSTS

To evaluate healthcare costs, the internal accounting and billing systems within hospitals will be utilized to estimate direct costs based on Cost Per Patient (CPP) principles for individual treatments and/or Diagnosis-Related Groups (DRG) for surgery and fertility treatment. We will also obtain CPP and/or DRG-based cost data from the hospitals where the included women receive care in connection with surgery, fertility treatments, pregnancy, childbirth, and postpartum follow-up. In addition, data on employment status at baseline will be collected. Quality-Adjusted Life Years (QALY) will be computed using data from the EQ-5D instrument. Variations in changes to health status and quality of life will be utilized for a cost-utility analysis, with the results presented as an Incremental Cost-Effectiveness Ratio (ICER). This analysis will provide insights into the additional cost per year of full health achieved with first line surgery compared to first line ART.

INDIRECT COSTS

To assess indirect costs related to the disease, both study arms will be examined with regard to estimating productivity costs, specifically the level of decline in production. Methods such as the friction cost method may be employed for this purpose.

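### Costs are counted to the study-level end of trial, but EQ-5D stops at each woman's three-year contact, so the cost and QALY windows do not match and the ICER may be biased

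*Protocol*

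**What the plan says.** **Cost window.** STUDY OBJECTIVES (definition of secondary outcome measures) sets it as "Health care costs from randomization to end of trial". HEALTH ECONOMICS includes care for surgery, fertility treatment, pregnancy, childbirth and the postpartum period.

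**End of trial.** STUDY ENROLLMENT gives the only definition: "The study will end when all patients enrolled in trial have been followed for 3 years after first treatment", or have withdrawn consent or been lost. The same section defines the start per patient: "Start of trial will be defined as start of first treatment which will be either surgery or first ART cycle".

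**QALYs.** HEALTH ECONOMICS states: "Quality-Adjusted Life Years (QALY) will be computed using data from the EQ-5D instrument". STUDY OBJECTIVES adds that the calculation draws on fertility status measures, with EQ-5D supplying the valuations. No time horizon is stated for the QALYs or the ICER.

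**EQ-5D schedule.** STUDY OBJECTIVES says: "The assessments are performed maximum one month before the first intervention, at the time of oocyte retrieval, two months after ART or surgery and at" the three-year follow-up. The SCHEDULE OF EVENTS TABLE places that last contact three years after first treatment. PATIENT REPORTED OUTCOMES places it elsewhere: "Visit, phone call or questionnaire 3 years after randomization".

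**Timing.** The SYNOPSIS gives three years of inclusion and three of follow-up, six in all. STUDY TREATMENT says that the time from randomisation to first treatment "should be minimized with a goal of three months and should preferably not exceed six months".

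**The concern.** The cost side and the health side of a cost-utility analysis should cover the same period for each woman. Here the cost window ends on a calendar date shared by the whole study, so a woman enrolled early contributes more years of cost than one enrolled late. Utility measurement ends for each woman at about three years. The starts differ too: costs begin at randomisation, while the first EQ-5D comes after randomisation and at most one month before first treatment.

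What is at stake is the incremental cost per QALY, which is a secondary, exploratory result. If the arms differ in cost after the last EQ-5D, that difference enters the numerator and nothing corresponding enters the denominator. Pregnancy and delivery costs are the obvious candidates, because the protocol counts them and because the arms are expected to differ in live births (55% against 71% in the sample size section). The two dates for the last EQ-5D are a contradiction on any view.

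**Working it through.** **Inputs.** Inclusion 36 months and follow-up 36 months (SYNOPSIS). Wait L from randomisation to first treatment of 0, 3 or 6 months; 3 and 6 come from STUDY TREATMENT, and 0 is the value implied by the six-year total. Accrual is assumed uniform over 36 months, because the protocol gives no accrual curve.

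**1. The plan's own figure.** 36 + 36 = 72 months = 6 years. This reproduces the stated duration, with no allowance for the wait.

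**2. Cost window, literal reading.** The trial ends at T = 36 + L + 36 months after the first randomisation. A woman randomised at month m has a cost window of T − m. With m uniform on 0 to 36, mean m = 18.

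| L (months) | T (months) | Range of T − m (months) | Mean (months) | Mean (years) |
|---|---|---|---|---|
| 0 | 72 | 36 to 72 | 72 − 18 = 54 | 4.50 |
| 3 | 75 | 39 to 75 | 75 − 18 = 57 | 4.75 |
| 6 | 78 | 42 to 78 | 78 − 18 = 60 | 5.00 |

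Individual windows therefore run from 3.0 to 6.5 years. If accrual is weighted late (mean m = 24), the means are 4.0, 4.25 and 4.5 years. If it is weighted early (mean m = 12), they are 5.0, 5.25 and 5.5 years.

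**3. EQ-5D window.**
- Last contact dated from first treatment: 36 to 37 months, or 3.0 to 3.08 years.
- Last contact dated from randomisation: (36 − L) to (36 − L + 1) months. For L = 3 this is 33 to 34 months (2.75 to 2.83 years). For L = 6 it is 30 to 31 months (2.5 to 2.58 years).

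**4. Unmatched time.**
- At the end, last contact dated from first treatment: T − (m + L + 36) = 36 − m, so 0 to 36 months, mean 18.
- At the end, last contact dated from randomisation: T − (m + 36) = 36 + L − m, mean 18 + L, so 18 to 24 months.
- At the start: L − 1 to L months. For L = 3 this is 2 to 3 months; for L = 6, 5 to 6 months. With a wait of a month or less there need be no start gap.

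**5. Per-patient reading, for comparison.** If end of trial meant each woman's own three-year point after first treatment, the cost window would be 36 + L = 39 to 42 months (3.25 to 3.5 years) for L = 3 to 6. With the last EQ-5D at the same point, the only gap left is at the start: 39 − 37 = 2 months up to 42 − 36 = 6 months.

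**6. Can relevant cost fall after year three?** STUDY TREATMENT allows up to three cycles of typically two to nine months each, and says surgery delays ART by two to three months. At the upper end, three cycles take 3 × 9 = 27 months. Adding 9 months of pregnancy (an assumption) gives 36 months in the ART arm and 36 + 2 to 36 + 3 = 38 to 39 months in the surgery arm. Some deliveries can therefore fall at or beyond the last EQ-5D. The protocol gives no unit costs and no distribution of delivery dates, so the cost involved cannot be calculated.

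**The case against.** **A per-woman reading of end of trial is possible.** Start of trial is defined per patient, and costs begin at a patient-level event. This reading is weaker than the literal one. The protocol has a separate per-patient term, end of follow-up, which it uses for live birth, spontaneous pregnancy and miscarriage, whereas costs use the term that is defined at study level. The possibility still means that 4.5 to 5 years is a consequence of one reading plus uniform accrual. It is not a figure in the protocol.

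**An ICER is a ratio of between-arm differences.** A reader might infer that the ratio divides 4.5 to 5 years of cost by 3 years of health. It does not. Allocation is 1:1 in permuted blocks within centre, so enrolment dates, and with them window lengths, should be balanced. Cost common to both arms cancels. This stands: only differential cost outside the EQ-5D window matters. Balanced windows do not, however, make late costs equal between arms.

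**QALYs are not said to stop at year three.** That is inferred from the questionnaire schedule. Fertility status also feeds the QALYs, and extrapolation could be set in an analysis plan that is not shown. This stands as a caution. The cost window, though, is already written in the protocol, and an analysis plan that cut costs at three years per woman would depart from it.

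**Months are not money.** With at most three cycles, most surgery and ART cost should fall within three years. This stands, so the share of calendar time that is unmatched must not be read as a share of cost.

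**The baseline timing is deliberate.** PATIENT REPORTED OUTCOMES explains that the first questionnaire is placed a similar time before treatment in both arms. The randomisation section also has eligibility entered one month before first treatment, which would nearly close the start gap. The start gap is therefore the smaller part of the problem.

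**Conclusion.** The point holds as a mismatch that the protocol itself fixes. Followed literally, individual cost windows run from about 3 to 6.5 years according to enrolment date, with a mean of about 4.5 to 5 years under uniform accrual and 4.0 to 5.5 years if accrual is skewed. EQ-5D covers about 3.0 to 3.1 years if the last contact is dated from first treatment, or about 2.5 to 2.8 years if it is dated from randomisation after a 3- to 6-month wait. The two dates for the last EQ-5D contradict each other whichever reading of end of trial is taken.

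The ICER may be biased by differential cost outside the EQ-5D window. Neither the size nor the direction can be derived from the document. A reader might infer that late obstetric cost will necessarily count against surgery. That is not shown, since more births after surgery could also fall inside year three. Nor does it follow that the cost-effectiveness objective cannot be answered: provided the hospital accounting and billing records are dated, costs can be cut at any horizon.

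The primary outcome is untouched and the analysis concerned is exploratory. The correction is still worth making now, because it changes a stated rule and is cheap.

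**What to change.** - In the definition of health care costs, replace the end of trial with each woman's own three-year date.
- State one origin and the same window for costs and QALYs. There are two workable choices. First treatment matches the clock of the primary outcome and nearly matches the baseline EQ-5D, but leaves out costs during the wait. Randomisation keeps those costs, but no EQ-5D is collected then, so the protocol must state that the baseline value is carried back to randomisation.
- Give the last EQ-5D the same date in the SCHEDULE OF EVENTS TABLE and in PATIENT REPORTED OUTCOMES, consistent with the chosen origin.
- Report costs after the three-year date separately, as a sensitivity analysis outside the base-case ICER.

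**Cost.** The change is one of wording plus, if randomisation is chosen, one stated assumption. Less cost data need be extracted for the base case. The downside is that costs after year three, including some deliveries of pregnancies that began within it, leave the base case. The sensitivity analysis is there to show what they would add.

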# STUDY DESIGN

An open label randomized controlled trial.

# STUDY FLOW CHART

# SCHEDULE OF EVENTS TABLE

| Procedures | **Baseline** | **Enrolment** | **1 month prior to surgery or start of first ART cycle^1^** | **Surgery^2^** | **2 months postoperative visit^2^** | **1:st oocyte retrieval** | **2 months after 1:st oocyte retrieval** | **2:nd oocyte retrieval** | **2 months after 2:nd oocyte retrieval** | **3:rd oocyte retrieval** | **2 months after 3:rd oocyte retrieval** | **Visit, phone call or questionnaire 3 years after first treatment (surgery or first ART cykle)** |
| --- | --- | --- | --- | --- | --- | --- | --- | --- | --- | --- | --- | --- |
| **Informed consent oral and written** | x |  |  |  |  |  |  |  |  |  |  |  |
| **Demographics** |  |  | x |  |  |  |  |  |  |  |  |  |
| **Record ultrasound and/or MRI staging according to AAGL and #ENZIAN staging system** | x |  |  |  |  |  |  |  |  |  |  |  |
| **Randomization** |  | x |  |  |  |  |  |  |  |  |  |  |
| **Record surgical procedure according to AAGL and #ENZIAN staging system** |  |  |  | x |  |  |  |  |  |  |  |  |
| **Record intraoperative complications^3^** |  |  |  | x |  |  |  |  |  |  |  |  |
| **Hospital stay** |  |  |  | x |  |  |  |  |  |  |  |  |
| **Record 8 weeks postoperative complications^4^** |  |  |  |  | x |  |  |  |  |  |  |  |
| **EHP-30, EQ5D and NRS scale^5^** |  |  | x |  | x | x | x | x | x | x | x | x |
| **Primary outcome (CLBR)** |  |  |  |  |  |  |  |  |  |  |  | x |
| **Secondary outcome/IVF cycle^6^** |  |  |  |  |  |  | x | x | x | x | x | x |

^1^ start of FSH injections ^2^only first line surgery group ^3^According to Classic ^4^According to Clavien Dindo ^5^Endometriosis Health Profile and Numeric Rating Scale ^6^LBR, PR, number of oocytes retrieved, fertilization grade, number of blastocysts

# TIMELINE

[figure not shown]

# STUDY ENROLLMENT

SCREENING PROCEDURE AND PARTICIPANT IDENTIFICATION

All women with stage III-IV AAGL endometriosis with infertility referred and/or eligible for surgery and/or ART-treatment such as IVF or ICSI will undergo screening for this trial. The results of this screening will be documented in a screening log. After obtaining oral and written informed consent, patients will be registered and randomized. Registration data will be entered to an electronic Case Report Form (eCRF).

STAGING

At baseline, a specialized transvaginal and abdominal ultrasound examination, supplemented with transabdominal ultrasound if indicated will be performed according to the International Deep Endometriosis Analysis (IDEA) group recommendations (25) to identify endometriosis lesions. Ultrasound and, if needed, magnetic resonance imaging (MRI) findings will be classified using the #ENZIAN and AAGL classification system (4, 6)**.**

The presence of adenomyosis will also be documented and characterized according to the Morphological Uterus Sonographic Assessment (MUSA) group recommendation (26, 27) . Women with and without suspected adenomyosis will receive the same treatment protocols. Presence of adenomyosis will not influence allocation but will be considered during the discussion of the final analysis of study results.

The use of hormonal treatment for endometriosis, prior to the surgery/ first ART-treatment or between the surgery and ART-treatment, will be documented and considered in the discussion of the outcomes.

INCLUSION CRITERIA

- Age 18 - 38 years old
- Endometriosis AAGL stage III-IV
- Referred or eligible for ART-treatment such as IVF or ICSI, independent of infertility diagnosis (28) (including sperm donation cycles for social reasons) and/or infertility due to dyspareunia/dysmenorrhea caused by endometriosis
- Body mass index 18-35 kg/m^2^
- Patients who have signed an approved Informed Consent

EXCLUSION CRITERIA

- Previous surgery for endometriosis except diagnostic laparoscopy.
- Previous IVF/ICSI-cycles (including prior fertility preservation cycles)
- Hemato- and/or hydrosalpinx
- Clear indication for surgery such as ureteral stenosis or intestinal sub-occlusive symptoms
- Suspicion of malignancy
- Submucosal fibroids (The International Federation of Gynecology and Obstetrics (FIGO) 0-1, any size) or intramural fibroids (FIGO 2-5, > 4 cm largest diameter of the largest myoma) (29)
- Uterine malformations (class U1-U6 according to ESHRE/ESGE-classification) (30)
- Patients with contraindications to surgery
- Patients undergoing ART with donated oocytes

RANDOMIZATION

After verification of eligibility, signed informed written consent participants will be randomly assigned to either undergo first-line ART or first-line surgery, followed by ART by equal allocation, 1:1. The randomization procedure will be stratified for participating center (permuted block design). Randomization will be performed at each site using the web-based instrument Red Cap. All inclusion criteria and no exclusion criteria must be met. One month before first treatment (IVF or surgery), inclusion and exclusion criteria are entered into the randomization/registration application RedCap. Patients withdrawn from the study after randomization but before treatment will be substituted by newly enrolled patients. Patients withdrawn from the study after first treatment will not be substituted. Username and password are required to log in; each investigator authorized to register patients has a personal login username and password. If all criteria are met, patients are registered, and the allocated patient number is recorded in the patients’ medical file.

There could be some uncertainty surrounding participants' willingness to engage in a Randomized Controlled Trial (RCT) comparing two fundamentally distinct approaches. Therefore, we intend to offer women who fulfill eligibility criteria but decline randomization the opportunity to take part in a parallel study – a prospective cohort study, that would provide valuable real-world outcomes of two different approaches to treatment of endometriosis -associated infertility. This parallel study will evaluate identical outcomes to those in the randomized trial. However, instead of random assignment, participation decisions will be made by the patients themselves, resulting in what is commonly referred to as a patient preference trial.

DEFINITION START OF TRIAL

Start of trial will be defined as start of first treatment which will be either surgery or first ART cycle (e.g start of FSH injections).

DEFINITION END OF TRIAL

The study will end when all patients enrolled in trial have been followed for 3 years after first treatment, withdrawn consent, or are lost to follow-up. Data from study participants that are lost to follow will be included in the final analysis. The trial steering committee may end enrolment at any time if it is deemed that this is in the best interest of the patients.

